# The effectiveness of a 6-week biofeedback gait retraining programme in people with knee osteoarthritis: protocol for a randomised controlled trial

**DOI:** 10.1186/s12891-023-07098-y

**Published:** 2023-12-19

**Keywords:** Knee osteoarthritis, Knee loading, Gait retraining, Biofeedback, Biomechanics, Stair, Sit-to-stand

## Abstract

**Background:**

Gait retraining is a common therapeutic intervention that can alter gait characteristics to reduce knee loading in knee osteoarthritis populations. It can be enhanced when combined with biofeedback that provides real-time information about the users’ gait, either directly (i.e. knee moment feedback) or indirectly (i.e. gait pattern feedback). However, it is unknown which types of biofeedback are more effective at reducing knee loading, and also how the changes in gait affect pain during different activities of daily living. Therefore, this study aims to evaluate the acute (6 weeks of training) and chronic (1 month post training) effects of biofeedback based on personalised gait patterns to reduce knee loading and pain in people with knee osteoarthritis, as well as examine if more than one session of knee moment feedback is needed to optimise the gait patterns.

**Methods:**

This is a parallel group, randomised controlled trial in a symptomatic knee osteoarthritis population in which participants will be randomised into either a knee moment biofeedback group (*n* = 20), a gait pattern biofeedback group (*n* = 20) or a control group (*n* = 10). Supervised training sessions will be carried out weekly for six continuous weeks, with real-time biofeedback provided using marker-based motion capture and an instrumented treadmill. Baseline, post-intervention and 1-month follow-up assessments will be performed to measure knee loading parameters, gait pattern parameters, muscle activation, knee pain and functional ability.

**Discussion:**

This study will identify the optimal gait patterns for participants’ gait retraining and compare the effectiveness of gait pattern biofeedback to a control group in reducing knee loading and index knee pain. Additionally, this study will explore how many sessions are needed to identify the optimal gait pattern with knee moment feedback. Results will be disseminated in future peer-reviewed journal articles, conference presentations and internet media to a wide audience of clinicians, physiotherapists, researchers and individuals with knee osteoarthritis.

**Trial registration:**

This study was retrospectively registered under the International Standard Randomised Controlled Trial Number registry on 7th March 2023 (ISRCTN28045513).

## Background

Knee osteoarthritis (KOA) is a common musculoskeletal disease which can have a significant impact on physical function and quality of life, especially in older populations [1]. Low-level micro-damage to intra-articular structures can be managed and regenerated in healthy populations, however, once the cartilage begins to degenerate due to excessive or uneven loading in people with KOA, the joint responds negatively to the compressive forces by further increasing joint loading, which accelerates the progression of KOA [2]. Sub-optimal gait patterns prior to injury, or an injury-induced gait pattern, may lead to greater knee loading on the affected side and a shift in the specific loading area of the cartilage [2]. Therefore, increased knee mechanical loading has a strong correlation with the progression of the disease [3, 4], and therapeutic intervention for KOA should focus on reducing knee loading during activities of daily life.

Previous research has found that knee moments, primarily in the frontal plane, have a strong correlation to knee joint contact forces [5, 6]. Considering that the majority of knee loading is distributed on the medial compartment, knee adduction moment (KAM) has become a common surrogate for knee joint contact force during movement [7, 8]. Recent studies have demonstrated that knee flexion moment (KFM) can also be a dominant predictor of the lateral knee joint contact force in both KOA and healthy populations [9]. Therefore, reducing the magnitude of knee moments in both frontal plane and sagittal plane during daily activities should be a target in research and clinic rehabilitation.

Gait retraining has been used as an effective, non-invasive strategy to slow down the progression of KOA by reducing the magnitude of knee loading [10]. Previous studies have reported the benefits of a smaller foot progression angle (FPA) for reducing the first peak KAM in both healthy and KOA populations [11, 12]. Greater step widths have been shown to reduce both first and second peak KAMs during walking and stair climbing by reducing the frontal plane ground reaction force moment arm length [13–16]. Finally, smaller step lengths have been found to reduce the peak KAM and KAM impulse in healthy weight and obese adults and KOA population [17–19]. Due to the complexity of walking and various anatomical differences between people, reducing knee loading using a fixed FPA is unlikely to be achievable, and thus a combination of FPA, step width and step length would likely facilitate a personalised gait modification that is comfortable and effective at reducing knee loading [20].

To enhance the performance and learning effect of gait retraining, biofeedback has been employed to provide real-time body information using visual and haptic interfaces [10, 21–23]. By interacting with the live feedback through changes in body position, participants learn how to modify and control their body movement during a motor task, which is gradually internalised over time [24]. Biofeedback is generally employed in two forms; direct feedback provides information about the target outcome itself, in this case knee loading, which participants need to reduce; while indirect feedback provides information about other outcomes such as FPA, step width and step length, which could affect the desired target outcome (i.e. knee loading). Direct feedback has been found to have a better effect on skill learning and retention compared to indirect feedback [25, 26]. however, previous evidence was based on healthy participants [23, 27], and no experimental study has compared different types of feedback in parallel. In addition, while knee loading may be the most effective feedback method in research, it is currently impossible to provide this type of feedback outside a lab setting. Therefore, it is important to explore the effectiveness of indirect feedback (gait pattern) methods that are more feasible in a day-to-day clinical and home settings.

This study will primarily explore the effectiveness of gait pattern feedback to reduce knee loading and knee pain during a 6-week gait retraining programme, and knee moment feedback group will be exploratory to identify the number of sessions needed to determine the optimal gait pattern over 6 weeks. In a long-term gait retraining programme, the gait patterns identified in the first session may not be optimal due to familiarisation with the environment, skin markers and desired gait alterations, as well as any learning effect or muscle activation adaptations [28]. Therefore, this study will explore if a participant’s optimal gait pattern changes or improves over time when provided with direct knee moment feedback, and how many sessions are required to identify a stable optimised gait pattern. Furthermore, there have not been any studies exploring the translative effect of gait retraining intervention into daily activities other than walking (e.g. sit-to-stand or stair climbing). Addressing these knowledge gaps in the literature will produce quantifiable outcome measures to identify and support the implementation of gait retraining for future clinical rehabilitation in KOA populations.

The primary objective of this study is to compare the effectiveness of gait pattern feedback to a control group, during a 6-week gait retraining programme in a KOA population. The secondary objectives are as follow:Explore the evolvement of gait patterns (FPA, step width and step length) when using knee moment biofeedback over time.Determine the optimal number of knee moment biofeedback sessions to identify the best combination of gait patterns (FPA, step width, step length) and quantify individual differences in the timescale for adaptation.Compare the similarity between gait pattern feedback and knee moment feedback to reduce KAM and pain.Explore and compare the successful internalisation of these two types of biofeedback gait retraining over time, through dual tasks, muscle activation and one-month gait retention.Explore the translative effect of these biofeedback gait retraining programmes on general daily activities.

## Methods

### Study design

This is a parallel group, randomised controlled trial, where participants will be randomly allocated into three groups; knee moment biofeedback group, gait pattern biofeedback group and control group. In participants with bilateral KOA, the most painful knee will be studied. The primary outcome will be KAM, while knee pain and functional ability will be considered secondary. All other outcomes will be exploratory outcome variables. The primary comparison will be between gait pattern feedback group and control group, while the comparison between gait pattern feedback group and knee moment feedback group will be exploratory.

### Recruitment and consent process

Participants will be recruited through NIHR Clinical Research Network, local hospitals, and social media. Clinical participants will be identified through routine consultations, physio classes, and patient database search. General public participants will be recruited through advertisements from the University website, social medial platforms, and by word of mouth. Interested participants will contact the research team, followed by further eligibility screening by the researcher. A participant information sheet will be emailed to eligible participants, and a written informed consent will be obtained by the researcher.

### Patient and public involvement

This study was conducted as part of our Versus Arthritis Centre for Sport Exercise and Osteoarthritis Research (CSEOR) and developed in accordance with the our Patient and Public Involvement (PPI) strategy [29]. The specific study protocol and biofeedback methods were co-developed with local patients and therapists and reviewed and endorsed by our national CSEOR PPI Advisory Panel. We will continue to collate participant feedback on patient experiences throughout the trial ensuring that we capture comments related to future improvements to overcome barriers to engagement, training delivery and adverse effects. This will help to understand and improve current and future intervention study designs.

### Study population/sample size

A sample size calculation was performed based on randomisation with stratification. Using an alpha level of 0.05, a power of 0.8, and an effect size estimates of 1.01 for KAM based on a previous gait retraining study with a similar design compared to our primary comparison (gait pattern group vs control group) [22]. Given that the comparison between gait pattern group and knee moment group is a secondary objective and no study has done the similar design, we will stick with the sample size needed for our primary objective. Seventeen participants are required for each experimental group. Thus, a total of thirty-four participants are needed to adequately power the study and detect significant differences in KAM between groups. Using a conservative estimate of twenty percent drop-out rate, the aim is to recruit twenty participants per group. For control group, we used an allocation ratio of 2:1 requiring recruitment of ten participants. This unequal allocation ratio for control group has been shown to increase the amount of data in the intervention groups where individual responses are likely more variable [30, 31]. In total, this study will recruit fifty participants.

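### The 80% power claim rests on 17 versus 17, but the primary comparison recruits 20 versus 10; on the same basis power is about 71%, or 61% after drop-out

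*Protocol article*

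**What the plan says.** Study design in the protocol article states: "The primary comparison will be between gait pattern feedback group and control group". The comparison of the two feedback groups with each other is called exploratory there.

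Study population/sample size gives the inputs: "Using an alpha level of 0.05, a power of 0.8, and an effect size estimates of 1.01 for KAM". The effect size is taken from an earlier gait retraining study "with a similar design compared to our primary comparison (gait pattern group vs control group"). Because the comparison between the two feedback arms is secondary, the authors write that "we will stick with the sample size needed for our primary objective".

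The result is: "Seventeen participants are required for each experimental group. Thus, a total of thirty-four participants are needed to adequately power the study". Two sentences then turn this into recruitment targets:

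- The target for the intervention arms allows for loss to follow-up: "Using a conservative estimate of twenty percent drop-out rate, the aim is to recruit twenty participants per group"
- The target for the comparator is half as large: "For control group, we used an allocation ratio of 2:1 requiring recruitment of ten participants"

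The stated reason for the smaller control group is that unequal allocation yields more data in the intervention groups, where responses are expected to vary more. Power is not recalculated for the unequal split. Randomisation confirms 2:2:1, and the Abstract confirms 20, 20 and 10. The model in Statistical analysis limits the group factor of the primary comparison to gait pattern and control, at baseline and post-training.

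**The concern.** The calculation is attached to gait pattern versus control, but the required 17 plus 17 is then allotted to the two biofeedback arms. Control, which is half of the primary comparison, gets ten. The total of 34 can be reached only by counting the knee moment arm, which contributes nothing to the primary test.

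There is also a smaller slip. Twenty recruits with 20% loss leave 16, which is below the plan's own requirement of 17.

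This is the only comparison the trial is powered for, and Statistical analysis bases the trial's primary success on KAM reduction from week 0 to week 6. If power is overstated, a non-significant result will be taken as firmer evidence against the intervention than it is.

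**Working it through.** **Inputs, all from the protocol article.** From Study population/sample size: effect size d = 1.01, alpha 0.05, target power 0.80, 17 required per group, 20% drop-out, 20 recruited per intervention group and 10 in control. From Study design and Statistical analysis: the primary comparison uses the gait pattern and control groups only. The sidedness of alpha is not stated.

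**Method.** Two-sample t-test with the noncentral t distribution:

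- noncentrality = d × √(n₁n₂/(n₁+n₂))
- degrees of freedom = n₁ + n₂ − 2
- power = probability that |t| exceeds the two-sided 5% critical value

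**Step 1: reproduce the plan's figure.** For 17 versus 17, n₁n₂/(n₁+n₂) = 289/34 = 8.5, so the noncentrality is 1.01 × 2.915 = 2.945 on 32 df, and power is 81.5%. For 16 versus 16 it is 78.9%. Seventeen is therefore the smallest equal arm that reaches 80%. A one-sided 5% test would need only 13 per arm, so the plan's 17 implies a two-sided test with equal arms.

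**Step 2: apply the same calculation to the arms that are compared.**

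| Gait pattern vs control | n₁n₂/(n₁+n₂) | Noncentrality | df | Power |
|---|---|---|---|---|
| 17 vs 17 (as calculated) | 8.50 | 2.945 | 32 | 81.5% |
| 20 vs 10 (as recruited) | 6.67 | 2.608 | 28 | 71.1% |
| 16 vs 8 (after 20% drop-out) | 5.33 | 2.332 | 22 | 60.6% |

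The drop-out row uses 20 × 0.8 = 16 and 10 × 0.8 = 8. The normal approximation gives 74.2% and 64.5% for the last two rows, which leads to the same conclusion. In precision, 20 versus 10 is worth about 13 per arm (2 × 6.67), and 16 versus 8 about 11 per arm (2 × 5.33).

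**Step 3: effect detectable with 80% power.** Solving for d gives 1.12 at 20 versus 10 and 1.27 at 16 versus 8, against the assumed 1.01.

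**Step 4: what an exact 2:1 split would need.** 24 versus 12 gives 79.3% and 26 versus 13 gives 82.5%, so 26 and 13 evaluable participants are required. Inflating for drop-out, 26/0.8 = 32.5 and 13/0.8 = 16.25, which means 33 and 17 recruited.

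**Step 5: drop-out inflation.** 17/0.8 = 21.25, which rounds up to 22 recruits, not 20. Taken alone in equal arms, the shortfall costs about 2.5 points (81.5% to 78.9%). Most of the loss in Step 2 comes from the control arm of ten.

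**The case against.** Four points can be made for the plan.

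**The planned analysis is not a plain t-test.** It is a mixed model with baseline and week 6, a group-by-time term and a participant intercept, which amounts to comparing changes. The article does not say whether 1.01 is standardised on post-training values or on change. If it is on change, 71% and 61% stand. If it is on post-training values, the effect on the change scale is 1.01/√(2(1−ρ)), where ρ is the baseline-to-week-6 correlation (not stated in the article, so the values here are assumptions). Power at 20 versus 10 and at 16 versus 8 is then 57% and 47% for ρ = 0.3, 71% and 61% for 0.5, 80% and 70% for 0.6, and 90% and 82% for 0.7. True power could thus be higher or lower. This part stands as a caveat on the exact figures. It does not rescue the plan's statement, which takes no credit for baseline and matches a plain t-test.

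**The test might be one-sided.** Then 20 versus 10 would reach 81.6%. But one-sided testing does not reproduce 17, and after the planned drop-out it gives only 73.1%.

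**Unequal allocation was deliberate and is disclosed.** The choice is legitimate. Carrying over a power figure from equal allocation is not. Greater variability in the intervention arm would reduce the cost of 2:1, but no standard deviations are given.

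**Intention-to-treat keeps everyone.** Even with no data lost, power on this basis is 71.1%.

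**Conclusion.** The concern holds. The article sizes the trial for gait pattern versus control at 17 per arm, then recruits 20 and 10 for that comparison and keeps the 80% claim. On the basis that reproduces its own 17, power is 71.1% with complete data and 60.6% after its own drop-out rate. The chance of missing the assumed effect is therefore about 29% to 39%, not 20%.

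These figures assume a two-sided 5% t-test with d = 1.01 and equal variances, and no gain from the baseline measurement. A strong baseline correlation could raise power and a weak one could lower it, but the article claims neither. The contradiction between 34 required and 30 recruited needs none of these assumptions. The inflation error is real but minor.

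**What to change.** Rewrite the power statement in Study population/sample size for the arms in the primary comparison:

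- State that, on a two-sided t-test at alpha 0.05 and d = 1.01, 20 versus 10 gives about 71% power with no drop-out, and 16 versus 8 gives about 61% after 20% drop-out. At 16 versus 8, 80% power is reached for an effect of about 1.27.
- Delete the claim that 34 participants across two experimental groups power the study for the primary comparison.
- State the sidedness of alpha. If credit is to be taken for the baseline measurement, state the scale of the 1.01 and the correlation assumed.
- If the 17-per-arm calculation is kept for reference, give its inflated size as 22. Once that basis is dropped, this correction has no further role.

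This is wording only and leaves the total of 50 unchanged. The cost is a less favourable published power.

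Re-allocating within the 50 (gait pattern 20, control 20, knee moment 10) would give 87.5% with full data and 78.9% at 16 versus 16. It is a trade-off, not part of the correction: it needs an amendment, halves the arm on which several secondary objectives depend, and is possible only if recruitment still allows.

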### Eligibility criteria

Inclusion criteria:Clinical diagnosis of KOA.Aged between 45 and 69 years.BMI ≤ 40.0 kg/m^2^.Current knee pain (minimum numeric rating score 2).Be able to walk without an assistive device for at least 15 consecutive minutes.

Exclusion criteria:Body mass index (BMI) > 40.0 kg/m^2^.Valgus knee alignment > 5° (this will be assessed in the baseline assessment session).History of knee replacement or tibial osteotomy.Conditions other than KOA that could affect walking (e.g. amputation, severe back pain, severe peripheral vascular or heart disease and neurological or developmental disease or lower limb surgery within the past 6 months);Inability to adopt an altered gait due to previous injury or surgery.Use of any orthotic equipment.Corticosteroid injection or oral intake within the past 6 weeks.Participation in a new structured exercise program or other treatment for KOA within the past 3 months, or planning to commence in the next 3 months.

### Randomisation

After the baseline assessment, participants will be randomly allocated (2:2:1) to the knee moment biofeedback group, gait pattern biofeedback group or control group, using a block randomisation plan by the researcher. Blinding is not achievable in this intervention study, and therefore neither participants nor researcher will be blinded.

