### Overview of the programme

Participants in the intervention groups will attend the lab a total of nine times, while the control group will attend a total of seven times. Firstly, all participants will attend the baseline assessment session (week 0a), after which a randomisation procedure will be carried out where participants will be randomly allocated to each group. Then, participants in the intervention groups will attend a biofeedback identification session in the same week (week 0b) to identify their optimal gait patterns. From week 1 to week 6, participants will start the weekly gait training sessions. Intervention groups will have real-time biofeedback along with treadmill walking, while the control group will perform treadmill walking for the same length of time without any instruction or feedback. The last training session (week 6) will finish with the post-training assessment session. Finally, a retention assessment session will be carried out one month later (week 10) for the two intervention groups only. Between the post-training assessment session (week 6) and follow-up assessment session (week 10), there will be no training or instructions of any kind provided. Figure 1 details the trial flow chart.

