### Biofeedback identification session

This session (Fig. 1) will only be conducted in the two intervention groups, and both intervention groups will receive knee moment feedback to identify their optimal gait patterns. Reflective markers and EMG electrodes will be attached. Participants will be instructed to walk on the instrumented treadmill and try various gait patterns (FPA, step width and step length), aiming to reduce the real-time knee moments graphs shown on the screen in front of them. They will first be instructed to try different FPAs, then try different step widths and finally different step lengths, to identify their optimal values for each gait parameter. Then, participants will be given 5 min to explore a combination of gait patterns that can consistently keep the knee moment graphs at a low level, in a symmetric, pain free and sustainable method. This 5-min period will be recorded to identify the FPA, step width and step length that most effectively reduces KAM for each individual.

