#### Gait pattern biofeedback gait retraining group

Real-time feedback of their live gait patterns (FPA, step width and step length) graphs with their personalised gait pattern target and their visual skeleton will be presented on the screen in front of the treadmill through the Visual 3D real-time plugin (C-Motion, Inc.) (Fig. 3). The participants individualised gait pattern target will depend on the outcomes from the identification session (week 0b, Fig. 1), which will be the same during each training session. Participants will be told to match the target as much as possible.

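### Feedback type is allocated openly before an identification session that both feedback arms share; withholding it until that session is recorded would remove an avoidable risk to the exploratory feedback comparison (optional)

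*Protocol article*

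**What the plan says.** The protocol article fixes the order of events in two places. The section on randomisation has this: "After the baseline assessment, participants will be randomly allocated (2:2:1) to the knee moment biofeedback group, gait pattern biofeedback group or control group". It also names the method and who applies it, in these words: "using a block randomisation plan by the researcher". The same paragraph says that neither side is blinded. Under Overview of the programme, the week 0a baseline assessment is followed by allocation ("after which a randomisation procedure will be carried out where participants will be randomly allocated to each group"), and then "participants in the intervention groups will attend a biofeedback identification session in the same week (week 0b) to identify their optimal gait patterns".

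The section on the identification session says that "both intervention groups will receive knee moment feedback to identify their optimal gait patterns". Both arms explore the three gait parameters in the same order and then have five minutes of free exploration: "This 5-min period will be recorded to identify the FPA, step width and step length that most effectively reduces KAM for each individual".

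The arms use the result differently. For the gait pattern arm, "The participants individualised gait pattern target will depend on the outcomes from the identification session", and that target stays the same in every training session. The knee moment arm trains instead towards a 10% reduction in first peak KAM, and its gait pattern is allowed to change over the six weeks.

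Comparing the two feedback types on KAM and pain is the third secondary objective (Background). Study design calls the comparison exploratory, and Statistical analysis assigns it to a repeated measures Bland–Altman analysis with no covariate named.

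**The concern.** Up to the end of week 0b the two feedback arms receive the same thing. They first differ at week 1. Yet by week 0b the researcher has allocated the feedback type, and nothing in the text keeps it from the participant or from whoever runs the session.

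The session depends on effort: the participant searches for a gait that lowers KAM while being instructed. For one arm the result will be the target for six weeks; for the other it sets no fixed gait target. People who know this have a reason to treat the session differently. If they do, the two programmes differ in something other than feedback type, and the comparison of feedback types absorbs that difference.

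There is also a smaller, lost opportunity. The KAM reduction reached at week 0b is a direct reading of how far a person can lower KAM. Measured after open allocation, it is not a clean covariate for comparing the feedback arms.

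**Working it through.** **Sequence.** Set side by side, the sections give:

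| Step | Gait pattern arm | Knee moment arm | Control | Section |
|---|---|---|---|---|
| Week 0a | baseline assessment | same | same | Overview |
| After 0a | open allocation | open allocation | open allocation | Randomisation, Overview |
| Week 0b | knee moment feedback, 5 min recorded | same | does not attend | Identification session |
| Weeks 1–6 | fixed gait target from 0b | KAM target, pattern may change | walking without feedback | Training sections |

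The visit counts agree. Intervention arms: 1 (0a) + 1 (0b) + 6 (training) + 1 (week 10) = 9. Control: 1 + 6 = 7.

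**Is the early allocation needed?** Controls do not attend week 0b, so feedback or control must be known after week 0a. Nothing in the shared session requires the feedback type. The statement that blinding is not achievable holds for training, where the screens differ. It does not hold for a session that is the same in both arms.

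**Does a later opening change the design?** Opening feedback versus control (4:1) and then feedback type (1:1) gives 4/5 × 1/2 = 2/5 for each feedback arm and 1/5 for control. Of 50 that is 20, 20 and 10, as planned.

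**Precision.** The plan states no precision for the feedback comparison. Its 17 per group belongs to the primary comparison (a two-sided t-test at d = 1.01 gives 16.41, rounded up to 17), and nothing here depends on it.

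Inputs: 20 per feedback arm, or 20 × 0.8 = 16 after the plan's 20% drop-out; and r, the correlation between the week 0b KAM reduction and the week 0 to 6 change in KAM. The documents do not give r, so 0.3 to 0.7 is an assumed range.

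The 95% half-width for the difference in mean KAM change, in SD units, is:

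- unadjusted: t(0.975, 2n − 2) × √(2/n)
- adjusted: t(0.975, df) × √[(2/n)(1 − r²)(1 + 1/(df − 1))], with df = 2n − 3; the last factor allows for chance covariate imbalance.

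At n = 16, unadjusted: 2.042 × √0.125 = 0.722. Adjusted with r = 0.5: 2.045 × √(0.125 × 0.75 × 1.0357) = 0.637.

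| n per arm | unadjusted | r = 0.3 | r = 0.5 | r = 0.7 |
|---|---|---|---|---|
| 20 | 0.640 | 0.620 | 0.563 | 0.464 |
| 16 | 0.722 | 0.702 | 0.637 | 0.526 |
| sample-size equivalent, 1/(1 − r²) | 1 | 1.10 | 1.33 | 1.96 |

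These figures credit the covariate with all of r. Baseline KAM will explain part of the same variation, so the added gain is smaller.

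**Why the covariate is unsafe in the present order.** If knowing the arm shifted the week 0b response by δ SD between arms, adjusting for it would move the contrast by about r × δ. For an assumed δ of 0.2 that is 0.3 × 0.2 = 0.06 to 0.7 × 0.2 = 0.14 SD. This is an illustration, not an estimate.

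**The case against.** The other side has a good deal in its favour.

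- **No error is shown.** Randomising after baseline and before any part of the intervention is conventional, and the section on the delayed control intervention treats the identification session as part of the programme. No statement in the protocol is wrong or contradictory. This stands, and is why the point is optional.
- **Bias is conjecture.** Both arms follow one set procedure. Knee moment participants are rehearsing the feedback they will train with, so they might try harder rather than less. This stands: neither the size nor the direction is known. The incentive to treat the session differently remains.
- **Disclosure is inferred.** The text says when allocation happens and that nobody is blinded, not when participants are told. The inference is reasonable because the researcher allocates before week 0b, but it is an inference.
- **The covariate serves no planned analysis.** Bland–Altman is planned for this comparison, and the one model formula given is for gait pattern versus control. Week 0b is also treadmill walking under live feedback, whereas the assessments use overground walking at preferred gait, so r may be low. This stands; the covariate is an extra.
- **Telling participants only part of their allocation is not enough.** The researcher holds the block plan and would still know the arm. This stands, and the fix has to deal with it.

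A reader might also infer that a weak week 0b in the knee moment arm distorts the objectives on how gait evolves and how many sessions are needed. The documents do not support this. Statistical analysis compares gait patterns within that arm from week 1 to week 6 and at follow-up. Where it refers to all time points, the only pre-training one it names is week 0, and the week 0 assessment precedes allocation. These are also within-arm questions, which a difference between arms at week 0b does not confound.

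**Conclusion.** The point holds as an avoidable risk, not as a demonstrated bias. The order of events and the absence of blinding are explicit, the session is shared, and its consequences differ by arm. Only the exploratory gait pattern versus knee moment comparison is exposed.

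A reader might extend this to the primary contrast; that would be wrong. For gait pattern versus control, the identification session is part of the treatment being tested, and controls have no such measurement to lose.

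The size of any bias is unknown. The possible precision gain at 16 versus 16 runs from trivial (0.72 to 0.70 SD) to useful (0.72 to 0.53 SD) over an assumed range of r, and is smaller once baseline KAM is in the model. The conclusion rests on one inference, that feedback type is known in practice at week 0b. Severity: optional improvement.

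**What to change.** Keep the 2:2:1 list, the 50 participants and intention-to-treat, and conceal the list in two sealed parts:

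1. After week 0a, open only whether the person is in feedback or control.
2. Open the feedback type, to participant and researcher alike, only when the week 0b recording is complete and the gait target has been computed for that person.
3. Whoever runs week 0b must not be able to see the second part. Sealed envelopes prepared by an existing member of the supervisory team would do. That person should also not know the block size, since the last feedback allocation in a known block can be deduced.
4. Anyone lost before the second opening stays in the listed arm.

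Optionally, any model comparing KAM change between the two feedback arms can then adjust for the week 0b KAM reduction alongside baseline KAM.

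Cost: a second disclosure step, someone to prepare the sealed list, and targets computed for knee moment participants who will not train to them. No extra visits or participants are needed. The trial was registered retrospectively, so recruitment may already have begun. In that case the change applies only to the remaining participants, and the report should give the date of the change.
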